## Abstract

**Background **Disability is prevalent in individuals with multiple sclerosis (MS), leading to difficulty in care access, significant caregiver burden, immense challenges in self-care and great societal burden.  Without highly coordinated, competent and accessible care, individuals living with progressive MS experience psychological distress, poor quality of life, suffer from life-threatening complications, and have frequent but avoidable healthcare utilizations. Unfortunately, current healthcare delivery models present severe limitations in providing easily accessible, patient-centered, coordinated comprehensive care to those with progressive MS. We propose a home-based comprehensive care model (MAHA) to address the unmet needs, challenges, and avoidable complications in individuals with progressive MS with disabling disease.

**Objective **The article aims to describe the study design and methods used to implement and evaluate the proposed intervention.

**Method** The study will use a randomized controlled design to evaluate the feasibility of providing a 24-month, home-based, patient-centered comprehensive care program to improve quality of life, reduce complications and healthcare utilizations overtime (quarterly) for 24 months. A transdisciplinary team led by a MS-Comprehensivist will carry out this project. Fifty MS patients will be randomly assigned to the intervention and usual care program using block randomization procedures. We hypothesize that patients in the intervention group will have fewer complications, higher quality of life, greater satisfaction with care, and reduced healthcare utilization. The proposed project is also expected to be financially sustainable in fee-for-service models but best suited for and gain financial success in valued-based care systems.

**Discussion** This is the first study to examine the feasibility and effectiveness of a home-based comprehensive care management program in MS patients living with progressive disability. If successful, it will have far-reaching implications in research, education and practice in terms of providing high quality but affordable care to population living with severe complex, disabling conditions.

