**Specific Aim 3**: To evaluate the feasibility of the MAHA model.

1)Acceptability by assessing patient and family experience with the program, as well as provider satisfaction2)Utility by examining the actual use of the program and number of referral received by other providers3)Implementation by evaluating the amount and type of resources needed to implement and factors affecting implementation;4)Adaptation by evaluating the selected elements of the program delivered by tele-health is as effective as face-to-face format.5)Financial sustainability and cost saving by comparing the estimated total cost of the program and financial compensation from payers.

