### Sample size

The sample size estimation is computed based on
**Specific Aim 1**: the increased score of quality of life (QoL) and
**Specific Aim 2**: the reduced number of unplanned healthcare utilizations associated with complications. An estimated 50 patients per group will provide 80% power to detect a 5-point difference [Usual Care mean (SD): 45(8.6), MAHA mean (SD) 50(8.6)] between groups in the SF-36 Mental Health Component Score QoL. This sample size also provides 80% power at a 5% significance level to detect a 34% reduction in unplanned visits/admits (from 2.5 per person per year to 1.65, using the Poisson distribution, which is most appropriate for count/rate data). These are feasible and clinically important differences. Based on our preliminary analyses, 125 patients are currently expected to meet these criteria. Furthermore, based on our previous patient survey results, a high proportion of patients (~80% or n = 100) have expressed a genuine interest in participating in MS research for the benefit of others with this disabling disease. Furthermore, we estimate 50 patients will be a reasonable panel size for the MS-Comprehensivist or care team leader (CTL) in the MAHA model (unpublished report).

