### Data collection, instruments and sources of data

Key data collection instruments, assessments, and measures are summarized in
Table 1. This information will be collected from three data sources: 1) patient reports to CRC personnel, 2) patient reports to the CTL or other MAHA team member at each home visit, and 3) medical record review.

**Table 1. T1:** Study measures.

Data Collection Instrument/Assessment		Method, Location, Data Source	Measure Timeline (in months)								
			BL*	3	6	9	12	15	18	21	24
Kurtzke Expanded Disability Scale (EDSS)		Neurologist/CTL to assess in person	X				X				X
PATIENT REPORTED MEASURES											
-Demographics		CRC to collect at baseline visit and via mail/phone	X								
-Functional activity of daily livings (ADLs) (Barthel) ^42^			X	X	X	X	X	X	X	X	X
-Multiple Sclerosis QoL Inventory (MSQLI) ^43^			X				X				X
-Novak Caregiver Burden Inventory (CBI) ^44^			X	X	X	X	X	X	X	X	X
-Client Satisfaction Questionnaire (CSQ-8) ^45^			X		X		X		X		X
POTENTIAL COMPLICATONS											
-Pneumonia -Urinary Tract Infection (UTI)	-Falls -Pressure Ulcer	CRC to collect at baseline visit, via mail/ phone and from medical record review. Providers assess during in-person visits	X	X	X	X	X	X	X	X	X
HEALTH SERVICES USE											
Emergency Room (ER) -Unplanned (acute)	Inpatient Admissions -Planned (elective) -Unplanned (acute) -Length of Stay	CRC to collect at baseline visit and via mail/phone. Providers assess during in-person visits. Data are retrieved from medical record.	X	X	X	X	X	X	X	X	X
CPT Codes and Reimbursement Amounts		UNMC Neurology Clinic Database	X		X		X		X		X
MAHA RESOURCE INTENSITY											
-Home visit time logs -On-call activity logs -Coordination care management activities		MAHA staff to document after each home visit and on-call activity	X	X	X	X	X	X	X	X	X

**Baseline questionnaires will be performed at the baseline clinic visit*

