***Specific Aim 3.*** To assess the acceptability, utility, implementation and adaptation of the program, we will create a toolkit that comprehensively describes our program structure, processes, patients/provider/system outcomes, as well as lessons learned. This toolkit will serve to evaluate the MAHA program and identify system-, provider-, and patient-levels of barriers and facilitators. To evaluate financial sustainability, we will specifically track the Current Procedural Terminology (CPT) codes for evaluation and management visits (clinic and home visits), care coordination, and care plan oversight. Reimbursement amounts associated with these codes will be summed for each study group at six and 12 months. T-tests and log transformed linear regression models will be used to compare total reimbursement amounts between groups. Also, staffing and associated salary estimates will be computed based on home visit time logs maintained by the MAHA team members, on-call activity logs, and number of home visits in the intervention group. We will project the necessary percent FTE and salary to execute the intervention model based on a range of panel sizes (e.g., 25, 50, 100 patients) per MS-Comprehensivist/CTL. The ratio of total salary costs-to-reimbursement amount for a given number of patients will be calculated for each group and compared using t-tests.

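### Reimbursement is compared by t-test and by log-transformed regression with neither given priority, and only the t-test targets the dollar totals that financial sustainability depends on

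*Protocol article*

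**What the plan says.** All references are to the protocol article.

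- **The question.** The Background lists, under Specific Aim 3: "Financial sustainability and cost saving by comparing the estimated total cost of the program and financial compensation from payers".
- **The outcome.** Under Data analysis, Specific Aim 3, the tracked procedure codes cover "evaluation and management visits (clinic and home visits), care coordination, and care plan oversight". Then: "Reimbursement amounts associated with these codes will be summed for each study group at six and 12 months". Table 1 gives the source as the "UNMC Neurology Clinic Database" and includes a baseline collection.
- **The comparison.** "T-tests and log transformed linear regression models will be used to compare total reimbursement amounts between groups". The sentence does not say which method leads, and it lists no covariates for the regression.
- **The related measure.** "The ratio of total salary costs-to-reimbursement amount for a given number of patients will be calculated for each group". This is also built from dollar amounts, and no log transformation is mentioned for it.

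**The concern.** Whether a programme pays for itself depends on dollars received against dollars spent. A group's total divided by its number of patients is the arithmetic mean, so that is the between-group quantity that matters here.

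The two named methods do not share this target. A t-test on dollars compares arithmetic means and keeps patients with a zero total. A linear model on log dollars, once exponentiated, gives a ratio of geometric means, and the log of zero does not exist. The two answers can therefore differ in size, in significance or in direction, and the text names both for the same comparison. What is at stake is how the reimbursement result is read: a significant log-scale result could be reported as a difference in money received when mean dollars are equal, or a real dollar difference could look like none.

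**Working it through.** **Inputs.** The article states no reimbursement mean, SD, share of zeros, expected difference or power, so there is no planned figure to reproduce. All distributional inputs below are assumptions. For group size, the Sample size section has "An estimated 50 patients per group will provide 80% power to detect a 5-point difference", while the Abstract has "Fifty MS patients will be randomly assigned to the intervention and usual care program" (25 per group if split equally). That difference is a separate matter, so both sizes are shown.

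**Step 1: unequal spread, no zeros.** If dollars are log-normal with arithmetic mean M and log SD s, the geometric mean is M × exp(−s²/2). For equal M in both arms:

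geometric-mean ratio (MAHA / usual care) = exp((s_UC² − s_MAHA²)/2)

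With assumed s_MAHA = 0.6 and s_UC = 0.9:

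exp((0.81 − 0.36)/2) = exp(0.225) = 1.25

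The true ratio of mean dollars is 1.00, yet the log model targets 1.25. With s equal in both arms the exponent is zero, and the two ratios agree.

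**Step 2: how often the tests would disagree.** Simulation with 3,000 runs per scenario and a two-sided 5% level. The methods are a Welch t-test on dollars and an unadjusted linear model on log dollars with zeros dropped. Assumed log SDs are 0.5 and 1.0 where the spread differs. Otherwise both are 0.7, and zeros, where present, are in one arm only.

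| Scenario | True position in dollars | Log model rejects (25 / 50 per group) | t-test rejects (25 / 50 per group) |
|---|---|---|---|
| No zeros, equal log SD | equal means | 5% / 5% | 5% / 5% |
| No zeros, log SD 0.5 vs 1.0 | equal means; geometric-mean ratio exp((0.25 − 1)/2) = 0.69 | 37% / 64% | 9% / 8% |
| No zeros, equal geometric means | mean ratio exp((1 − 0.25)/2) = 1.45 | 6% / 5% | 13% / 35% |
| 10–30% zeros, equal means among billed patients | mean lower by 10–30% in the arm with zeros | 4–5% / 4–5% | 7–31% / 9–49% |
| 10–30% zeros, equal overall means | equal means | 8–36% / 11–62% | 4–5% / 5% |

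**Reading.** Rows 2 and 5 show the log model finding a difference when mean dollars are equal. Rows 3 and 4 show it missing a real dollar difference. Row 1 shows that it is harmless when there are no zeros and spreads are similar. The t-test follows the dollar means throughout. Its rejection rate is somewhat above 5% in row 2, and its power is modest in rows 3 and 4.

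**The case against.** The strongest reply is that the dollar-scale comparison is already planned. The t-test is named first in the same sentence, keeps zeros and compares arithmetic means between randomised groups. The group sums and the salary-to-reimbursement ratio are dollar quantities too. A reader might infer that the log model decides sustainability; the text does not say so.

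A reader might also infer that zero totals are known or expected. They are not documented. Participants are recruited from the same neurology clinic whose database supplies the amounts, and usual care includes standard MS care. Zeros over six months remain possible, because only certain codes from one clinic count and the Background describes access to care as difficult, but no passage supports a particular share.

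Nor does the article call the regression the only adjusted analysis. It names no covariates there, and the adjustment wording in Data analysis belongs to Aims 1 and 2.

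Finally, zero handling, back-transformation and the order of precedence are details that a condensed article may leave to an analysis plan, and pairing a t-test with a log model is common for skewed costs. The absence of those details is no fault. What stands is the stated choice: a log-transformed model is committed to, on equal footing with the t-test, for a question about total dollars that it does not estimate.

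**Conclusion.** The point holds in a limited form. Of the two methods named for total reimbursement, the t-test matches the sustainability question and the log-transformed regression does not, and the text puts them side by side. The mismatch in target is certain. Whether it would change the result depends on unequal log-scale spread or unequal shares of zeros, neither of which the article reports. The ratio of 1.25 and the rejection rates illustrate assumed inputs and are not predictions for this trial. The stronger conclusion, that the planned analysis will misstate the programme's finances, is not supported, because the dollar comparison remains in the plan. Severity is minor: one component of a secondary feasibility aim.

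**What to change.** In Data analysis, Specific Aim 3, state that the difference in arithmetic mean reimbursement per patient is the deciding comparison. Estimate it by linear regression on untransformed dollars, adjusted for baseline reimbursement (already collected in Table 1), with bootstrap or robust confidence intervals. A generalised linear model with log link and robust standard errors is an acceptable alternative: it models the arithmetic mean and accepts zero totals. Drop the log-transformed model, or label it supportive and report its result as a ratio of geometric means.

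This needs no new data and changes only the analysis wording. The price is somewhat wider intervals when the dollar amounts are skewed.

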**Figure 2. f2:**
[figure not shown]
MAHA Model.

***MAHA Team Processes (10 C’s).*** The MS-Comprehensivist or CTL will be responsible to: 1) provide regular and frequent visits to patients’ homes using a pre-planned schedule based on each individual’s care needs; 2) coordinate patients’ care by collaborating and communicating closely with the core team partners, and “neighbors and best friends”; and 3) train the home health staff in the specialty care of MS patients. In the process of care, the MAHA model stresses patient/family engagement (i.e., informed and activated) and productive interaction between patients and providers through ten fundamental elements (10 Cs;
Figure 3).

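### The Aim 3 staffing and salary estimate leaves out the coordination record that Table 1 collects, while reimbursement includes coordination codes, so cost and revenue cover different activities

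*Protocol article*

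**What the plan says.** Four places in the protocol article bear on this.

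- **Data analysis, Specific Aim 3, cost side.** The text states that "staffing and associated salary estimates will be computed based on home visit time logs maintained by the MAHA team members, on-call activity logs", and the list closes with "and number of home visits in the intervention group". From these inputs the team will project percent FTE and salary for panels of, for example, 25, 50 and 100 patients, and form the ratio of total salary cost to reimbursement.
- **Data analysis, Specific Aim 3, revenue side.** The tracked billing codes are those for "evaluation and management visits (clinic and home visits), care coordination, and care plan oversight". The plan then says: "Reimbursement amounts associated with these codes will be summed for each study group at six and 12 months".
- **Table 1, MAHA Resource Intensity.** Three records are listed: "Home visit time logs -On-call activity logs -Coordination care management activities". All are scheduled at baseline and every three months to month 24. One collection method covers all three: "MAHA staff to document after each home visit and on-call activity".
- **MAHA Team Processes (10 C's).** The care team leader has three duties: home visits, coordination with the core partners and outside specialists and community resources, and to "train the home health staff in the specialty care of MS patients".

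Specific Aim 3, item 5, sets the target as the estimated total cost of the programme against what payers compensate.

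**The concern.** The salary estimate uses two of the three Table 1 resource records plus a visit count. A visit count carries no coordination time, so it does not stand in for the third record. The same paragraph counts the income that coordination and care plan oversight generate. As written, the ratio's numerator and denominator do not cover the same work, and the numerator falls short of the total programme cost that item 5 asks for.

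Coordination is one of the leader's three listed duties, so the omitted share may not be small. Two outputs are affected: the FTE projection by panel size, which another institution would use to staff the model, and the ratio that answers the financial sustainability question. Aims 1 and 2 are untouched.

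**Working it through.** The article states no salary, FTE, reimbursement or ratio figure, so there is nothing to reproduce. The check compares the lists and then works out the size of the effect.

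**Step 1: set the lists side by side.**

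| Activity | Recorded in Table 1 | Named as a salary/FTE input | Code counted in reimbursement |
|---|---|---|---|
| Home visits | yes | yes (time log and visit count) | yes |
| On-call work | yes | yes | no separate code named |
| Coordination and care management | yes | **no** | **yes** |
| Training of home health staff | not named | no | no |

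Only the coordination row has revenue counted without a named cost input.

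**Step 2: algebra.** Let S be the full staff salary cost, R the reimbursement, and c the share of S that is coordination time not captured in the visit or on-call logs.

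- Computed ratio = (1 - c) × S/R, so full ratio = computed ratio / (1 - c).
- Full FTE = computed FTE / (1 - c), taking the share of hours equal to the share of salary.

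**Step 3: numbers.** c is not in the article. The range below is an assumption.

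| c | Factor 1/(1 - c) | Full ratio if computed is 0.80 | Computed ratio if full is 1.20 | Full FTE if computed is 0.60 |
|---|---|---|---|---|
| 10% | 1.11 | 0.89 | 1.08 | 0.67 |
| 20% | 1.25 | 1.00 | 0.96 | 0.75 |
| 30% | 1.43 | 1.14 | 0.84 | 0.86 |
| 40% | 1.67 | 1.33 | 0.72 | 1.00 |

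The 0.80, 1.20 and 0.60 are illustrations, not plan figures. A full ratio of 1.20, a loss, would be computed as below 1 once c exceeds 1 - 1/1.20 = 16.7%.

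**Step 4: whose time c refers to.** The factor applies to the total-salary ratio only when c is a share of all staff salary time. Suppose instead that 40% of the leader's time alone is unlogged, and that the leader makes up half of the computed salary cost (also an assumption). The ratio is then multiplied by 0.5/0.6 + 0.5 = 1.33, not 1.67, and a computed 0.80 becomes 1.07, not 1.33.

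**The case against.** **Coordination time may already be in the logs.** Table 1 puts the three records in one row with one instruction, to document after each visit and on-call activity. Staff may enter coordination work in the same session, and some or all of it could reach the salary estimate that way. This stands as a limit on size: c covers only time outside those logs. It does not remove the point, because Table 1 lists coordination as its own item, no text says that it is folded into the other two, and coordination between visits has no stated moment of recording.

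**An article condenses costing detail.** That would answer a complaint about silence. Here the article gives a specific input list that does not match its own table or its own billing codes.

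**The whole ratio need not be too favourable.** A reader might infer that the ratio is biased towards showing sustainability. The documents do not support that. Table 1 takes reimbursement only from the UNMC neurology clinic database, while the core team also includes the primary care provider and home health agencies. Income billed by those parties may fall outside that database, which would push the ratio the other way. Only the sign of the coordination component is established. The FTE projection does not use reimbursement, so this possible offset does not repair it.

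**Training does not fit the mismatch.** It is a leader duty and is missing from the salary inputs, but no training code is counted as revenue, and part of it may be a start-up cost that does not grow with panel size. It should not be added to c.

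**The reach is limited.** The article assigns implementation to the toolkit, and no decision threshold is attached to the ratio.

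**Conclusion.** The point holds as a mismatch of inputs. The stated basis for staffing, FTE and salary omits a record that the trial plans to collect, while revenue for the same activity is counted. For any c above zero, this component understates both the projected FTE and the salary-to-reimbursement ratio by the factor (1 - c). Over an assumed c of 10% to 40%, the full value is 1.11 to 1.67 times the computed one.

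That size rests on two assumptions: the value of c, which the article does not give, and c being a share of all staff salary time. If all coordination time is in fact recorded in the visit and on-call logs, the effect is zero, but the article does not say so. Neither the net direction of the whole ratio nor a complete loss of coordination time from the cost estimate can be concluded from the text. The matter should be corrected, since it bears on a named aim, but it does not touch the outcome comparisons.

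**What to change.** 1. In Data analysis, Specific Aim 3, compute staffing, FTE and salary from all three Table 1 resource records, and state that time already in a visit or on-call log is not counted again under coordination.
2. In Table 1, have coordination time logged when it occurs, not only after a visit or on-call activity.
3. Report FTE by panel size and the ratio on that basis, so that cost and reimbursement cover the same activities.
4. Report the leader's hours spent training home health staff as a separate cost line, since no listed code matches them.

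The coordination record is already planned, so the change is a sentence or two of analysis text, a logging instruction and one extra line for training hours. The downside is slightly more staff logging and a possibly less favourable ratio.

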## Methods

### Study design

The study is a prospective, two-group, randomized experimental design with nine data collection points (baseline and every three months). MS patients recruited from a neurology clinic will be randomized into two groups: the intervention or usual care group. The usual care group receives the current standardized MS care, while the intervention group receives usual care plus 24-months of the MAHA intervention provided by a transdisciplinary team led by a MS-Comprehensivist. The usual care group will receive the intervention at the end of the 24-month period if the intervention is found to be effective by our a priori criteria. The study is subject to review and approval by the University of Nebraska Medical Center Institutional Review Board (IRB) and informed consent will be obtained from all participants prior to the study.

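### The between-group t-test on the salary-to-reimbursement ratio has no stated usual-care salary input, so it is undefined or uninformative as written

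*Protocol article*

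**What the plan says.** The sub-aim is set out in the list under Specific Aim 3 in the Background: "Financial sustainability and cost saving by comparing the estimated total cost of the program and financial compensation from payers". It concerns the program's own cost and income.

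The Data analysis section (Specific Aim 3) then gives four steps.

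- Reimbursement: "Reimbursement amounts associated with these codes will be summed for each study group at six and 12 months", followed by "T-tests and log transformed linear regression models will be used to compare total reimbursement amounts between groups".
- Salary: staffing and salary estimates are to be computed from "home visit time logs maintained by the MAHA team members, on-call activity logs, and number of home visits in the intervention group".
- Projection: "We will project the necessary percent FTE and salary to execute the intervention model based on a range of panel sizes", with 25, 50 and 100 patients as examples.
- Comparison: "The ratio of total salary costs-to-reimbursement amount for a given number of patients will be calculated for each group and compared using t-tests".

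Table 1 lists the time, on-call and coordination records under MAHA resource intensity, with the method "MAHA staff to document after each home visit and on-call activity". The Study design section describes the arms: "The usual care group receives the current standardized MS care, while the intervention group receives usual care plus 24-months of the MAHA intervention".

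**The concern.** The comparison step needs a ratio in both arms, but the salary step supplies a numerator in only one. Usual-care patients generate reimbursement, so their denominator exists. The people who treat them keep no logs under this plan, and no other salary source is named for them. The wording also leaves open whether the ratio is a patient-level quantity or one figure for a panel. A t-test needs the former.

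This is the only planned test that sets salary cost against reimbursement. An analyst who follows the text would get no result, or a p-value that reflects how the ratio was built and not whether the program pays for itself. The abstract expects the program to be financially sustainable under fee-for-service, so a small p-value here could be taken as support for that expectation.

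**Working it through.** The article gives no expected value, standard deviation or power for this ratio, so there is no planned figure to reproduce. The check has two parts.

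**1. Which inputs exist in which arm**

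| Component | MAHA arm | Usual care |
|---|---|---|
| Reimbursement (denominator) | Tracked by CPT code | Tracked by CPT code |
| Staff time and salary (numerator) | Time logs, on-call logs, home visits | No source stated |
| FTE and salary projection | By panel size | Not described |

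In the salary sentence, the phrase restricting it to the intervention group could attach to home visits alone. That changes nothing, because the time logs are kept by MAHA team members and Table 1 assigns both the visit and the on-call records to MAHA staff.

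**2. What the t-test does under each reading**

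*Reading A: one ratio per group for a panel.* Degrees of freedom = n1 + n2 − 2 = 1 + 1 − 2 = 0. A single value has no within-group variance. Run on one value per group, the pooled and Welch tests both return an undefined t and p.

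*Reading B: one ratio per patient, usual-care salary not collected.* The MAHA arm has variance, but the usual-care ratio cannot be computed. There is no test.

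*Reading C: one ratio per patient, only MAHA salary counted.* Every usual-care ratio is 0, with mean 0 and variance 0. The Welch statistic reduces to

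t = mean / (SD / √n) = √n / CV,

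where mean, SD and CV (= SD / mean) describe the MAHA-arm ratios. It tests whether the mean MAHA ratio differs from 0, which is certain once any MAHA staff time is logged. Break-even is a ratio of 1, and 1 does not appear in the statistic.

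The CV is not in the article, so it is an assumption. Two arm sizes are shown because the abstract speaks of fifty patients in all and the Sample size section of 50 per group.

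| Assumed CV | n = 25: √25 / CV | n = 50: √50 / CV |
|---|---|---|
| 0.5 | 5 / 0.5 = 10.0 | 7.07 / 0.5 = 14.1 |
| 1 | 5 / 1 = 5.0 | 7.07 / 1 = 7.1 |
| 2 | 5 / 2 = 2.5 | 7.07 / 2 = 3.5 |

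The two-sided 5% critical values are 2.06 (24 df) and 2.01 (49 df), so every cell is significant. Two simulated data sets, drawn from a gamma distribution with shape 4 and scale 0.3 (mean 1.2, CV 0.5), gave t = 10.3 at n = 25 (sample CV 0.485; 5 / 0.485 = 10.3) and t = 18.6 at n = 50 (sample CV 0.381; 7.07 / 0.381 = 18.6), with p below 1e-9 in both. The assumed mean of 1.2 is a program that loses money. One that made money would give the same t for the same CV.

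**The case against.** The strongest reply is that the unit of analysis is ambiguous, and that a condensed article may leave it to the full plan. The reimbursement comparison is worded in much the same way: sums for each study group, then t-tests between groups. If that is accepted as a comparison of patient-level totals, the ratio deserves the same charity. This stands. The result of 0 degrees of freedom holds only under Reading A, although the reference to a given number of patients does lean that way. The missing usual-care numerator does not depend on this choice and defeats the test under the patient-level readings too.

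A second reply is that salaries are described as estimates, and CPT visit codes from the clinic database could support an estimate of usual-care staffing. That is possible, but the article does not propose it. The supportable statement is that no source is stated, not that usual care has no staff cost or that the cost could never be estimated.

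Two stronger readings are tempting. A reader might infer that financial sustainability cannot be assessed at all. The document does not support this: the sub-aim compares program cost with payer compensation, which needs no between-group ratio, and the reimbursement comparison and FTE projections are unaffected. A reader might also infer that the panel sizes of 25, 50 and 100 are to serve as t-test observations. Nothing in the text says so; they appear only as projection scenarios.

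**Conclusion.** The ratio comparison is wrong as written. With the inputs stated, the usual-care ratio is either undefined or zero by construction, and in neither case does a between-group t-test inform the sub-aim. Under the zero reading, t = √n / CV, which is 2.5 to 14.1 over assumed CVs from 2 to 0.5 and arm sizes of 25 and 50, whether or not the program covers its costs. Under the one-value-per-group reading there is also no variance and there are 0 degrees of freedom.

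The conclusion assumes that the salary inputs named in the Data analysis section and Table 1 are the complete list. If the full plan names a patient-level staff-cost source for usual care, the test becomes computable, though it would still answer a different question from the one in the sub-aim. The consequence is confined to one component of the feasibility aim. Aims 1 and 2 and the sample size do not depend on it.

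**What to change.** Replace the ratio sentence in Data analysis, Specific Aim 3, along these lines:

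- Drop the between-group t-test on the ratio.
- In the MAHA arm, report summed staff cost divided by summed reimbursement over the same period, and the net margin per patient (reimbursement minus staff cost). Give each a 95% interval, for example from a bootstrap that resamples patients. Read the ratio against break-even at 1 and the margin against 0.
- Keep the between-group comparison for reimbursement, and state that it uses patient-level totals.
- Present the 25, 50 and 100 panel projections as scenarios without p-values.

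If a between-group ratio is really wanted, patient-level staff cost must be defined and obtained in both arms, which means additional data collection or estimation.

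The change uses records the trial already plans to keep, but it is more than rewording. On-call and coordination time is shared, so the plan must state how it is allocated to patients, and the sponsor should confirm that the logs identify the patient. A patient-level bootstrap treats staffing as if it varied with each patient. It does not capture the fixed cost of an FTE that must be paid whatever the panel size, so the panel scenarios should show that cost.
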